### Population

Participants included in the study must meet the selection criteria listed below.

#### Inclusion criteria

The inclusion criteria for the study will be participants aged between 18 and 65 years; both sexes; complaint of low back pain lasting more than 3 months; magnetic resonance imaging findings of lumbar disc degeneration (LDD) performed less than 6 months before inclusion in the study; indication for open surgical treatment with isolated microdiscectomy or associated with lumbar arthrodesis; failure of conservative treatment for at least 6 weeks and/or progressive neurological deficit; agreement to follow all phases of the clinical investigation, having signed the informed consent form (ICF) for participation in the study.

#### Exclusion criteria

The exclusion criteria for the study will be a history of open lumbar spine surgery at any stage of life; chemotherapy or pulse therapy with corticoids; immune deficiency; previous intradiscal therapies (nucleotomy or discography); previous endoscopic surgery; history of spinal infection treated with antibiotics in the 6 months prior to inclusion in the study; use of antibiotics in the 2 months prior to the surgical procedure; incomplete research inclusion form; refusal to participate and/or sign the ICF.

### Patient and public involvement

Participant eligibility will be evaluated by the study researchers through a clinical interview and imaging exams evaluation, according to the participants’ interest and availability to participate in the study. If the patient agrees to take part in the study, the predetermined selection criteria will be used to evaluate them. The researchers will explain the details of the study and conduct a joint reading of the ICF. Questions about the study objectives, risks and benefits, stages, and research confidentiality will be answered. A patient will only participate upon signing the ICF at this stage of the research. A copy of this document will be given to the participant, another to the responsible researcher, and a third will be attached to the medical record. After signing the consent form, the patient will undergo an evaluation for demographic and clinical data collection and the forms developed for this purpose will be completed. If the patient is unable to read and sign the written consent form, researchers will verbally explain the study details and the patient will orally provide consent in the presence of a witness who will sign the consent form. The recruitment of participants will take place over a 6-month period, until 120 individuals are included, aiming at a minimum number of 96 collections.

### Participant allocation

The participants will be operated by the same surgical team, and the surgical technique will be posterior discectomy followed by arthrodesis of the approached segment.

#### Blinding

The results of microbiological cultures or molecular analysis will not be disclosed neither to the patients nor to the surgeons. The radiologist who will review the imaging tests will also be blinded to patient data and laboratory results. The researcher who will be analyzing the pain and function scores will be blinded as well.

### Withdrawal of a study participant

A participant will be removed from the study in cases of ICF withdrawal, death, recruitment failure identification, loss of post-surgical follow-up, or the presentation of clinical symptoms of infection, intense pain, fever without other infectious *foci*, increased erythrocyte sedimentation rate and/or C-reactive protein, leukocytosis, imaging tests compatible with spondylodiscitis, or any other condition that leads to blinding interruption.

The reason and circumstances of each participant’s withdrawal from the study will be detailed. The data gathered until the patient is withdrawn from the study will be included in the final analysis.

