Once LIVD colonization by *C*. *acnes* is confirmed using microbiological techniques, in the absence of clinical signs of infection, the main challenge is to understand the implications of this finding for homeostasis of that microenvironment. Rajasekaran et al. showed strong evidence of LIVD colonization by *C*. *acnes* using rDNA-16s PCR and proteomic analyses [29]. These authors discovered not only host defense proteins, but also proteins associated with bacterial viability and proliferation. Although these findings have demonstrated the active presence of *C*. *acnes* in intervertebral discs, definitively ruling out the possibility of contamination, they do not necessarily reflect the activity of the expressed proteins, which may remain inactive and without interference in pain-generating pathways and/or the inflammatory response.

In this context, the combined use of proteomic and metabolomic techniques to analyze LIVD colonized by *C*. *acnes* would be more appropriate in order to assess the subclinical consequences of the colonization by this pathogen [30]. These techniques have already been used successfully to define molecular signatures in other clinical settings [31–34], especially in chronic pain [35–40], and can also provide integrative information on cell function at the molecular level about the role of *C*. *acnes* in LDD and LBP [41–44].

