## Hypotheses and objectives

Our hypothesis is that LDD and LBP are related to LIVD colonization by *C*. *acnes*.

The primary goal of this study is to determine the incidence of LIVD colonization by low virulent pathogens using specific sampling and culture techniques, as well as phenotypic and genotypic techniques for microbiological characterization.

Other objectives of the study include: 1- assessing the possibility of clinical specimen contamination in positive cultures; 2- establishing a correlation between the presence of the pathogen and the clinical and radiological profile (Modic type 1 changes) of the study participants; 3- to outline a phylotypic profile of the most isolated *C*. *acnes* strains by bacterial WGS; and 4- identify a molecular profile for LDD and LBP in patients with positive cultures for *C*. *acnes* through proteomic and metabolomic techniques.

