#### Secondary outcomes

*Low back pain*. At the time of patient recruitment the Visual Numeric Scale (VNS) [[50]] will be used to assess LBP intensity and daily activity limitations. A 30% increase in baseline LBP in the first postoperative month will be considered clinically significant. The VNS and the visual analogue scale have a good correlation and are equally sensitive to quantifying postoperative pain [51].

*Quality of life*. The validated Portuguese version of the EuroQol questionnaire (EQ-5D) will be used to assess the quality of life of colonized and non-colonized groups with and without Modic changes [52]. The EQ-5D is a self-administrated standardized instrument containing five items (mobility, self-care, usual activities, pain/discomfort, and anxiety/depression).

*Functionality*. The functionality of the participants will be quantified through the validated Portuguese version of the Oswestry Disability Index (ODI) for LBP [53].

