### Adverse effects

Failures related to surgical treatment, such as surgical wound infection, CSF leak, deep vein thrombosis, pain recurrence, or any other adverse events that may arise in the postoperative period, will be reported and considered in data analysis.

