### Questionnaires

Questionnaires on pain (VNS), functionality (ODI), and quality of life (EQ-5D) will be given at recruitment as well as at 1, 3, and 6 months postoperatively. A professional who is not involved in the study will collect all questionaires. Follow-up clinical visits will be carried out at 1, 3, and 6 months postoperatively, with acceptance deviation of 7, 14, and 21 days, respectively.

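### Removal for intense pain, infection signs or raised inflammatory markers makes the 1-, 3- and 6-month scores missing in a way that depends on the outcome and possibly on colonization

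*Protocol article*

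**What the plan says.** The section Withdrawal of a study participant lists the reasons for removal from the study. After consent withdrawal, death and recruitment failure come "loss of post-surgical follow-up, or the presentation of clinical symptoms of infection, intense pain, fever without other infectious" foci, then "increased erythrocyte sedimentation rate and/or C-reactive protein, leukocytosis, imaging tests compatible with spondylodiscitis", and finally any other condition that breaks the blind. The items form an "or" list. None has a threshold or a time window. On data handling the section says: "The data gathered until the patient is withdrawn from the study will be included in the final analysis". It also says that the reason for each withdrawal will be documented.

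Secondary outcomes names low back pain on the VNS, quality of life on the EQ-5D (one of whose five items is pain/discomfort) and function on the ODI. For pain it adds: "A 30% increase in baseline LBP in the first postoperative month will be considered clinically significant". Under Questionnaires, all three instruments "will be given at recruitment as well as at 1, 3, and 6 months postoperatively".

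Hypotheses and objectives states: "Our hypothesis is that LDD and LBP are related to LIVD colonization by" *C. acnes*. The Introduction leaves open whether bacterial proteins found in the disc are active, or inactive and "without interference in pain-generating pathways and/or the inflammatory response".

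Adverse effects says that events in the following group will be reported and considered in the analysis: "Failures related to surgical treatment, such as surgical wound infection, CSF leak, deep vein thrombosis, pain recurrence".

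**The concern.** Intense pain is a high value of a secondary outcome. A rule that removes people for it stops measurement in those with the worst results. Infection signs, raised ESR or CRP and leukocytosis are possible consequences of the exposure under study. If the hypothesis is right, colonized participants will meet the triggers more often and lose more of their follow-up.

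Keeping earlier data limits the loss but does not remove it. Someone removed before month 1 contributes no postoperative score, and someone removed later contributes none from then on. The repeated-measures methods named in the Statistical analysis methodology (repeated-measures ANOVA, Friedman's test) in their standard form need every compared time point, so a participant removed after month 1 also drops out of the full-course analysis.

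At stake is the postoperative comparison of pain, function and quality of life between colonized and non-colonized participants.

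**Working it through.** **1. What is not affected.** The plan's own figure is the minimum of 96 for the incidence of colonization. With n = z²p(1−p)/d², z = 1.96, d = 0.10 and p = 0.5 (p is my assumption, the usual worst case; the article does not state it), n = 3.8416 × 0.25 / 0.01 = 96.04, so 96 reproduces. The recruitment target of 120 corresponds to 96/(1 − 0.20) = 120, an implied 20% allowance. Colonization is determined from specimens taken at surgery, and data up to withdrawal are kept, so neither figure is touched by a postoperative trigger. The same holds for associations with scores taken at recruitment.

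**2. How the trigger meets the outcome.** The clinically significant event is a 30% rise over baseline pain in month 1. For an assumed baseline of 6 or 7 on a 0–10 scale, that is 6 × 1.3 = 7.8 or 7 × 1.3 = 9.1. Participants who reach the event are therefore those most open to being classed as having intense pain.

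**3. Binary illustration (all rates assumed).** Let p be the true proportion who worsen and w the share of them withdrawn before the score is recorded. The observed proportion is q = p(1 − w)/(1 − pw). With p = 0.30 colonized and 0.15 non-colonized and w = 0.50:

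- colonized: 0.15/0.85 = 0.176
- non-colonized: 0.075/0.925 = 0.081
- observed difference: 9.5 points, against a true 15

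| w | Observed difference, true 15 points (30% v 15%) | Observed difference, true 10 points (20% v 10%) |
|---|---|---|
| 25% | 12.6 | 8.1 |
| 50% | 9.5 | 5.8 |
| 75% | 5.5 | 3.2 |
| 100% | 0 | 0 |

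**4. Continuous illustration (all values assumed).** VNS means 4 (colonized) and 3 (non-colonized), SD 2.5, scores limited to 0–10, which gives a true difference of about 0.91. Every score at or above the cut-off is removed (simulation, 2 million per group).

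| Cut-off | Observed difference | Share of true difference left | Removed, colonized v non-colonized |
|---|---|---|---|
| 9 | 0.83 | 92% | 2.3% v 0.8% |
| 8 | 0.76 | 84% | 5.5% v 2.3% |
| 7 | 0.67 | 73% | 11.5% v 5.5% |
| 6 | 0.55 | 60% | 21.2% v 11.5% |

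With means of 5 and 4 instead, no limits, and truncated-normal means μ − σφ(a)/Φ(a), where a = (cut − μ)/σ, a true difference of 1.00 becomes 4.451 − 3.707 = 0.745 (the two means are rounded) at a cut of 8, and 4.081 − 3.451 = 0.630 at a cut of 7. The direction is the same.

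**5. Withdrawal set beside Adverse effects.** One section removes participants who show infection or intense pain. The other says that wound infection and pain recurrence will be considered in the analysis. The triggering event can still be counted, because the reason for withdrawal is recorded. What happens to that participant afterwards cannot be analysed.

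**The case against.** The strongest counter-argument is a narrower reading of the list. It runs from infection symptoms to imaging of spondylodiscitis and closes with any other condition that breaks the blind, so the intended common thread may be suspected disc infection that requires unblinding. The Introduction frames colonization as occurring without clinical signs of infection, which gives some reason to set overt infection apart. This has weight, but the text does not say it: the items stand as separate alternatives, and intense pain alone suffices. Even the narrow reading removes participants for a possible consequence of colonization.

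It can also be said that the illustrations lie near a worst case. They delete every score above the cut-off, although a score taken at the visit where the event is found counts as gathered before withdrawal. That stands, and is why a range is given. More frequent removal among colonized participants is likewise assumed.

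A reader might infer several stronger conclusions that the documents do not support:

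- That the colonization–pain association as a whole is distorted. Only scores after withdrawal are at risk.
- That the adverse-event comparison is empty, or that the Adverse effects section is flatly contradicted. The triggering event can be reported, and pain recurrence is not the same term as intense pain. The two sections are in tension.
- That the protocol forbids later collection and nothing can be done in the analysis. It does not expressly forbid collection; it provides for none. With reasons recorded, sensitivity analyses for data missing not at random could bound the effect, though they cannot replace the scores.
- That withdrawal should be limited to consent withdrawal and death. Recruitment failure has nothing to do with this bias.

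**Conclusion.** The point holds for the secondary postoperative outcomes. Followed as written, the rule makes follow-up at 1, 3 and 6 months missing in a way that depends on the outcome and possibly on colonization. If colonized participants do have more pain, the comparison is probably biased towards no difference. This goes beyond detail that an analysis plan could supply, because the protocol itself fixes the rule and uncollected scores stay uncollected.

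The size cannot be derived from the documents, which give no threshold for intense pain, no group means and no SD. Under the assumptions shown, about 92% to 60% of a VNS difference remains for cut-offs from 9 down to 6. The binary result runs from a modest loss (15 to 12.6 points) to complete loss, depending on how many worsened participants leave before being scored.

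**What to change.** - Separate any clinical handling of these events from withdrawal from the study. No clinical rule is proposed here.
- Continue the already scheduled 1-, 3- and 6-month questionnaires in every participant who still consents.
- Record intense pain, infection signs, raised markers, leukocytosis and imaging findings as outcomes or adverse events, and analyse all participants with a culture result.
- Keep consent withdrawal, death and recruitment failure as withdrawal reasons.
- Flag participants who are unblinded or overtly infected, and exclude them only in a sensitivity analysis.
- Reconcile the withdrawal section with Adverse effects, so that the later course of participants with wound infection or pain recurrence can be analysed.

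The cost is an amendment of about one paragraph and no new visits. The small downside is a few self-reported scores collected after partial unblinding, which the flag handles.

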### Selection of outcomes

#### Primary outcome

The main objective of this study will be to determine the incidence of intervertebral disc colonization by *C*. *acnes* in patients with LBP and LDD. Positive cultures will be used to confirm colonization, followed by phenotypic and genotypic confirmation of the isolated pathogen by mass spectrometry (Biotyper) and rDNA-16s PCR analysis, respectively.

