**Fig 1 pone.0271773.g001:**
[figure not shown]
Flowchart showing all stages of the study.

The clinical specimens collected will be:

Peripheral blood. A 10 mL aliquot will be obtained 30 min after the infusion of surgical antibiotic prophylaxis through upper limb venoclysis. This sample will be placed in a tube containing clot activator for further separation of the serum, which, in turn, will be stored at −80°C for further analysis.Skin swab. After skin asepsis with 2% chlorhexidine gluconate degerming solution and 0.5% chlorhexidine gluconate alcoholic solution, a swab will be collected from the region where the surgical incision will be performed.Intervertebral disc. Five fragments will be collected at each level approached during surgery. A set of sterile surgical tweezers will be used exclusively for collection, one for each tissue fragment collected. The forceps with tissue fragment will be given to a member of the laboratory who will monitor the procedure inside the operating room immediately after collection. Each fragment will be placed in a vial containing thioglycolate broth (Merck^®^, Brazil) and 20 glass beads. The vials will be labeled with the initials of the study participants and the type of clinical specimen. After collection, the vials containing the clinical specimens will be kept at room temperature (18°C to 22°C) and transported in a specific case to the laboratory within a maximum period of 2 h.Muscle–ligament tissue. Before obtaining the LIVD fragments, five fragments of muscle–ligament tissue adjacent to the collected disc will be collected. The same collection and initial cooling precautions used for the disc fragments will be followed when collecting the adjacent tissue.

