### Laboratory analysis

#### Cultures

The skin swabs will be opened only in a laboratory setting. Samples will be seeded on blood agar plates (5% defibrinated sheep blood; blood agar base, 40 g/L; agar, 5 g/L) and anaerobic blood agar (5% defibrinated sheep blood; blood agar base, 40 g/L; agar, 5 g/L; hemin, 10 mL/L; menadione, 5 drops/L. After sowing in solid media, the swab will be inoculated in thioglycolate medium, where it will remain for 14 days. One of the plates will be incubated in a capnophilic atmosphere (5% to 10% CO_2_), while the other will be incubated in strict anaerobiosis (atmosphere containing 10% CO_2_,10% H_2_, and 80% N_2_) using an anaerobic chamber or Glove Box (Coy Labs^®^, USA).

The plates will be read after 24 h of incubation and, in case of growth, the colonies will be identified. In the absence of growth, they will be incubated again, and a new reading will be performed after 72 h. The thioglycolate vials containing skin swabs will be kept in a bacteriological incubator (35°C to 37°C) for 14 days. In a laboratory setting, the tubes containing disc fragments and muscle–ligament tissue will undergo vortexing (Even EVX2800-BI^®^, Brazil) for 15 s. All tubes will be kept in a bacteriological incubator (35°C to 37°C) and, after 24 h, the first subculture will be carried out using a 100 μL bacteriological loop. An aliquot of the thioglycolate will be taken and plated on blood agar and anaerobic blood agar. The first plate will be incubated in a capnophilic atmosphere and the second in strict anaerobiosis using an anaerobic chamber or Glove Box (Coy Labs^®^, USA). The plates will be read after 24 h and the colonies will be identified in case of growth. In the absence of growth, they will be incubated again, and a new reading will be performed after 72 h. The same procedure will be used for all thioglycolate vials (totaling six vials for each level approached). Thioglycolate tubes containing the clinical specimens will be kept in an oven for 14 days. Subcultures will be carried out after 72 h and always every 3 days, with the last subculture being carried out on the 14^th^ day of incubation in the same solid culture medium and atmospheres used in the first 24 h.

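### The primary case definition confirms the species of a disc isolate but not its origin, and the paired tissue and skin controls do not enter it, so any contamination counts as colonization

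*Protocol article*

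**What the plan says.** All references are to the protocol article.

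- **Primary outcome.** The target is the incidence of disc colonization by *C. acnes*. The case definition is "Positive cultures will be used to confirm colonization, followed by phenotypic and genotypic confirmation of the isolated pathogen by mass spectrometry", together with 16S PCR. It gives no minimum number of positive fragments and no condition on control specimens.
- **Hypotheses and objectives.** Contamination is listed among the other objectives: "assessing the possibility of clinical specimen contamination in positive cultures". Nothing states how the result of that assessment feeds back into the primary outcome.
- **Sampling (specimen list under Fig 1).** For the disc, "Five fragments will be collected at each level approached during surgery". For the control tissue, "five fragments of muscle–ligament tissue adjacent to the collected disc will be collected". For the skin, after asepsis, "a swab will be collected from the region where the surgical incision will be performed". For disc fragments, "Each fragment will be placed in a vial containing thioglycolate broth", and the control tissue is collected with the same precautions.
- **Cultures.** Disc and muscle–ligament tubes are vortexed, incubated and subcultured on one schedule. The count given is "totaling six vials for each level approached".
- **Statistical analysis methodology.** Binary colonization is the outcome of the logistic models. The Quality of life and Modic changes sections also compare colonized with non-colonized groups.

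**The concern.** The Introduction presents colonization versus contamination as the unresolved dispute in this field, with cited positivity running from 46% (anaerobes, 61 patients) down to 3.4% of discs. A definition that a skin contaminant can satisfy at every step cannot help settle that dispute. Mass spectrometry and PCR are both run on the cultured isolate. The media quality control checks sterility and recovery of the broth and plates, not the surgical field.

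Two things are at stake. First, the primary proportion mixes true colonization with contamination in unknown shares, and recruiting more participants does not reduce that error. Second, the same classification defines the groups for quality of life, Modic type 1 frequency and the logistic models. At fragment level it also separates the metabolomic samples with and without isolated *C. acnes*. Contaminated specimens would sit on the colonized side of the intended molecular signature.

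The vial count matters because the disc-versus-control comparison is informative only if both tissues have the same number of chances to turn positive.

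**Working it through.** **1. The plan's own precision figure.** Sample size calculation gives 95% confidence, a 10-point margin and n = 96. Taking p = 0.5 (not stated), n = 1.96² × 0.25 / 0.10² = 96.04, which reproduces 96. The concern does not affect this figure. The 10-point margin serves below as a yardstick.

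**2. Vial count.** Five disc plus five muscle–ligament fragments at one vial each is 5 + 5 = 10 per level. Cultures says six.

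**3. False positives per level if fragments are independent.** Let c be the per-fragment contamination rate. The documents give none, so 1%, 3% and 5% are assumed. The any-of-five reading gives 1 − (1 − c)⁵. A threshold of at least two of five gives 1 − (1 − c)⁵ − 5c(1 − c)⁴.

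| c | any of 5 | at least 2 of 5 |
|---|---|---|
| 1% | 1 − 0.9510 = 4.9% | 1 − 0.9510 − 0.0480 = 0.1% |
| 3% | 1 − 0.8587 = 14.1% | 1 − 0.8587 − 0.1328 = 0.8% |
| 5% | 1 − 0.7738 = 22.6% | 1 − 0.7738 − 0.2036 = 2.3% |

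If two levels are operated, any of ten gives 1 − (1 − c)¹⁰ = 9.6%, 26.3% and 40.1%.

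**4. Fully correlated fragments.** If all five fragments of a level are contaminated together or not at all, any-of-five and at-least-two-of-five both equal c. At c = 3% that is 3% under either rule, instead of 14.1% and 0.8%. The inflation is much smaller, and the fragment threshold removes none of it.

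**5. When the bias equals the planned margin.** With true colonization π, independent fragments, any-of-five and no lost true positives, the excess is (1 − π)[1 − (1 − c)⁵]. Setting this to 0.10 gives:

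- π near 0: c = 1 − 0.900^(1/5) = 2.1%
- π = 20%: c = 1 − 0.875^(1/5) = 2.6%
- π = 46%: c = 1 − 0.815^(1/5) = 4.0%

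**6. Why a threshold and a control rule are both needed.** Under independence, dropping discs whose patient has any positive among five control vials helps little. At c = 5%, false positives fall only from 22.6% to 0.226 × 0.774 = 17.5%. When the field itself is contaminated the controls do the work. If each fragment then picks it up with probability 0.2 (assumed), five control vials detect it with probability 1 − 0.8⁵ = 67%, and one vial with probability 20%.

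**7. What a 5-versus-1 split would do.** With no true colonization, c = 3% and independence, 14.1% of levels would be disc-positive and 3.0% control-positive. This applies only if six means five disc vials and one muscle–ligament vial.

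**The case against.** The strongest reply is that this is a condensed article. Positivity criteria may sit in the full protocol or analysis plan, and contamination is not ignored: it is a named objective with paired specimens collected for it. That disposes of any charge that the investigators overlooked contamination. It does not dispose of the main point, because the article states the primary case definition and the controls are not part of it.

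A reader might infer several stronger things that the documents do not support:

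- **That one positive vial suffices.** This is the natural reading where no threshold is given, but the text does not say so.
- **That the primary estimate is biased upward on balance.** Contamination pushes it up. The Sampling section has antibiotic prophylaxis start at anesthetic induction, before disc collection, which may lower recovery and push it down. The net direction is not fixed, although the two errors do not cancel patient by patient.
- **That 14% to 40% of participants would be false positives.** Those figures need assumed rates and independent fragments. Fragments share one incision, team and field, so some correlation is plausible. The low-end studies cited in the Introduction report total positivity of 3.4% of discs and 6 of 313 patients (1.9%). The number of multi-level patients is not given either.
- **That the control tissue is under-sampled.** Sampling plans equal numbers, and Cultures applies one procedure to all vials. Six could be five disc plus one muscle–ligament vial, five disc plus the skin-swab vial, or a misprint.

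It is also fair to say that the planned multiplex PCR targets virulence and oxidative genes and is not described as strain typing, and that a cutoff of two of five is a judgement.

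**Conclusion.** The concern holds in a limited form. Followed as written, the primary definition cannot tell a contaminant from a disc organism, and controls that could help are collected but not used in it. Any contamination that occurs is therefore counted as colonization, in the primary proportion and in the groups built on it.

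The size is unknown. On an any-of-five reading with per-fragment contamination of 1% to 5% (assumed), false positives per level lie between c itself under full correlation and 4.9% to 22.6% under independence. At the independent end, a rate of about 2% to 4% per fragment would match the whole planned margin of error.

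The disagreement between ten and six vials is a plain internal contradiction. It shows that the count must be reconciled. It does not show that the disc–control comparison is biased.

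**What to change.** 1. Before any culture is read, state the number of positive disc fragments per level that defines colonization. Two of five is one option.
2. State the rule by which *C. acnes* in the same patient's muscle–ligament or skin specimens reclassifies a positive disc as possible contamination. Where both disc and control grow, compare the isolates by whole genome sequencing.
3. Report the crude and the control-adjusted proportion side by side, and compare disc with muscle–ligament positivity within patients by a paired method such as McNemar's test.
4. Reconcile the vial count between Sampling and Cultures so that disc and muscle–ligament tissue are cultured in equal numbers at each level.

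**Cost.** This is mainly wording, since the specimens and sequencing of *C. acnes* isolates are already planned. Sequencing of control isolates for within-patient matching is not stated, so some extra sequencing may be needed. Some true low-load colonization will be classed as unconfirmed, and the headline figure may fall. A rule based on control positivity alone would also reclassify some truly colonized patients by chance: up to 22.6% of them at c = 5% with five independent control vials. That is the reason for comparing isolates and for keeping the crude proportion in the report.
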